#### **14.5 Quality Assurance Monitoring**

In accordance with federal regulations, the study sponsor is responsible for ensuring proper monitoring of an investigation and ensuring that the investigation is conducted in accordance with the protocol. Qualified monitors will oversee aspects of site conformity to make certain the site staff is operating within the confines of the protocol, and in accordance with GCP. This includes but is not limited to protocol compliance, documentation auditing, monitoring of drug disposition, and ensuring the informed consent process is being correctly followed and documented. Non-conformity with protocol and federal regulations will be reported as a protocol deviation and submitted to the study sponsor and study IRB of record, (as applicable), for further review.

#### **14.6 Participant and Data Confidentiality**

"Participant confidentiality and privacy are strictly held in trust by the participating investigators, their staff, the safety and oversight monitor(s), and the sponsor(s) and funding agency, and will be maintained in accordance with all applicable federal regulations and/or state/Commonwealth law and regulations. This confidentiality is extended to the data being collected as part of this study. Data that could be used to identify a specific study participant will be held in strict confidence within the research team. No personally-identifiable information from the study will be

released to any unauthorized third party without prior written approval of the sponsor/funding agency and the participant.

All research activities will be conducted in as private a setting as possible.

The study monitor, other authorized representatives of the sponsor or funding agency, representatives of the Institutional Review Board (IRB), regulatory agencies or representatives from companies or organizations supplying the product, may inspect all documents and records required to be maintained by the investigator, including but not limited to, medical records (office, clinic, or hospital) and pharmacy records for the participants in this study. The clinical study site will permit access to such records.

Participant records will be held confidential by the use of study codes for identifying participants on CRFs, secure storage of any documents that have participant identifiers, and secure computing procedures for entering and transferring electronic data. The study participant's contact information will be securely stored at each clinical site for internal use during the study. At the end of the study, all records will continue to be kept in a secure location for as long a period as denoted in Section 14.17, Records Retention and Requirements.

By signing the protocol signature page, the investigator affirms that information furnished to the investigator by NIDA will be maintained in confidence and such information will be divulged to the IRB/Privacy Board, Ethical Review Committee, or similar expert committee; affiliated institution; and employees only under an appropriate understanding of confidentiality with such board or committee, affiliated institution and employees.

#### **14.7 Certificate of Confidentiality**

To further protect the privacy of study participants, the Secretary, Health and Human Services (HHS), has issued a Certificate of Confidentiality (CoC) to all researchers engaged in biomedical, behavioral, clinical or other human subjects research funded wholly or in part by the federal government. Recipients of NIH funding for human subjects research are required to protect identifiable research information from forced disclosure per the terms of the NIH Policy (see <https://humansubjects.nih.gov/coc/index>). This protects participants from disclosure of sensitive information (e.g., drug use). It is the NIH policy that investigators and others who have access to research records will not disclose identifying information except when the participant consents or in certain instances when federal, state, or local law or regulation requires disclosure. NIH expects investigators to inform research participants of the protections and the limits to protections provided by a Certificate issued by this Policy."

#### **14.8 Health Insurance Portability and Accountability Act (HIPAA)**

Study sites may be required by their institutions to obtain authorization from participants for use of protected health information. Sites will be responsible for communicating with the IRB(s) or Privacy Board(s) of record and obtaining the appropriate approvals or waivers to be in regulatory compliance. Releases of participant identifying information that are permitted by the HIPAA regulations, but which are prohibited by other applicable federal regulations and/or state/Commonwealth law and regulation, are prohibited.

## **14.9 Investigator Assurances**

Each site must have on file an active Federalwide Assurance (FWA) with the HHS Office for Human Research Protection setting forth the commitment of the organization to establish appropriate policies and procedures for the protection of human research subjects in alignment with 45 CFR 46, Subpart A, with documentation sent to NIDA or its designee. Research covered by these regulations cannot proceed in any manner prior to NIDA receipt of certification that the research has been reviewed and approved by the IRB provided for in the assurance (45 CFR 46.103). Prior to initiating the study, the principal investigator at each study site will sign a protocol signature page and investigator agreement, providing assurances that the study will be performed according to the standards stipulated therein.

## **14.10 Financial Disclosure / Conflict of Interest**

All investigators will comply with the requirements of 42 CFR Part 50, Subpart F to ensure that the design, conduct, and reporting of the research will not be biased by any conflicting financial interest. Everyone with decision-making responsibilities regarding the protocol will confirm to the sponsor annually that they have met their institutional financial disclosure requirements.

## **14.11 DEA Registration**

All Drug Enforcement Administration (DEA) requirements must be met, including registration, inspection if required, and certification, as applicable. In order to receive shipments of study drug, sites must have a DEA registration (facility research registration or a practitioner registration) that has the address where study drug will be shipped on the registration. Additionally, dispensing any controlled substance requires a DEA registration unless exempt by federal or state law or pursuant to CFR Sections 1301.22-1301.26.

## **14.12 Investigational New Drug (IND) Requirements**

An IND application will be submitted to the FDA for this study. Any subsequent amendments to this clinical trial submitted to the FDA will reflect awareness of and compliance with 45 CFR 46 and its subparts, as well as the International Council for Harmonization Good Clinical Practice Guidelines (ICH E6 R2). This IND study will also be conducted in accordance with all applicable FDA regulations and will comply with all applicable laws and regulations at clinical research sites.

## **14.13 Clinical Monitoring**

Data completeness will be monitored weekly by review of aggregates/summaries of data completeness reports. The DSC will produce completeness summaries for DSMB meetings and for Trial Progress Reports, which are posted daily on the internet for perusal by study leadership.

The Lead Team comprised of the Lead Investigators (LI), Project Directors, and Site Principal Investigators (PI) team will provide oversight for the study at all sites, with input from the Local Node PIs, Lead Node PIs and the National Institute on Drug Abuse (NIDA) Center for Clinical Trials Network (CCTN) Scientific Officers and the DSC and CCC when required. Emmes will support study activities related to logistics (e.g., provision of study supplies and quality control) and data management. As the primary goal of this project is implementation, these monitoring

efforts will focus on research (data collection) procedures of the research staff and not on implementation procedures, processes or outcomes of other entities. Qualified research personnel from the Local Node may assist the Lead Investigators with site management during the study to encourage and assess compliance with the study protocol, GCP guidelines, and to ensure the integrity of the study progress. This will take place as specified by the Lead Investigators and will occur as often as needed to help prevent, detect, and correct research problems at the study sites. The Lead Team will verify that study research procedures are properly followed and that site research staff members are trained and able to conduct the research protocol appropriately. If review of study documentation indicates that additional training of study personnel is needed, the Lead Investigators and/or Local Node will see that it is done.

Protection of the rights and welfare of study participants will be a vigilant process conducted by the research teams at all sites, at the Lead Node and by the sponsors of the research. Monitoring of the study sites will be conducted on a regular basis using a combination of NIDA-contracted monitors and Lead Investigators staff. Site investigators will host periodic visits by monitors who will ensure all study procedures are appropriately conducted, and that study data are generated, documented and reported in compliance with the protocol, GCP, and applicable regulations. These monitors will audit at mutually agreed upon times, regulatory documents, case report forms (CRFs), and corresponding source documents for each participant. NIDA-contracted monitors will assure that submitted data are accurate and in agreement with source documentation where applicable and will also review regulatory/essential documents such as correspondence with the IRB. Areas of particular concern will be participant signed/dated consents, eligibility for study participation, protocol adherence, safety monitoring, IRB reviews and approvals, regulatory documents, participant records, and principal investigator supervision and involvement in the study. Reports will be prepared following the visits and forwarded to the Lead Investigators and Site PIs the Lead Node, local node and NIDA CCTN.

Local quality assurance (QA) monitor visits will take place as specified by the Lead Investigators and visits will occur as often as needed to help prevent, detect, and correct problems at the study sites. The Lead Investigator's team will work in collaboration with Emmes staff to ensure that study procedures are properly followed, and that site staff are trained and able to conduct the protocol appropriately. If the Lead Investigator's team review of study documentation indicates that additional training of study personnel is needed, the Lead Investigators to determine course of action.

#### **14.14 Inclusion of Women and Minorities**

The study sites should aim and take steps to enroll a diverse study population. If difficulty is encountered in recruiting an adequate number of women and/or minorities, the difficulties involved in recruitment will be discussed in national conference calls and/or face-to-face meetings, encouraging such strategies as linkages with medical sites and/or treatment programs that serve a large number of women and/or minorities, advertising in newspapers or radio stations with a high female/minority readership/listening audience, etc.

### **14.15 Prisoner Certification**

As per 45 CFR 46 Subpart C, there are additional protections pertaining to prisoners as study participants. A prisoner is defined as any individual involuntarily confined or detained in a penal institution. The term is intended to encompass individuals sentenced to such an institution under a criminal or civil statute, individuals detained in other facilities by virtue of statutes or commitment procedures which provide alternatives to criminal prosecution or incarceration in a penal institution, and individuals detained pending arraignment, trial, or sentencing. In order to meet these additional protections, the study team will obtain certification from the Office for Human Research Protections (OHRP) to [enroll prisoners and] follow-up with participants who become prisoners during the course of the study, as necessary.

### **14.16 Regulatory Files**

The regulatory files should contain all required regulatory documents, study-specific documents, and all important communications. Regulatory files will be checked at each participating site for regulatory document compliance prior to study initiation, throughout the study, as well as at study closure.

### **14.17 Records Retention and Requirements**

Research records for all study participants (e.g., case report forms, source documents, signed consent forms, audio and video recordings, and regulatory files) are to be maintained by the investigator in a secure location for a minimum of 3 years after the study is completed and closed. These records are also to be maintained in compliance with IRB, state and federal requirements, whichever is longest. The Sponsor and Lead Investigator must be notified in writing and acknowledgment from these parties must be received by the site prior to the destruction or relocation of research records.

### **14.18 Reporting to Sponsor**

The site principal investigator agrees to submit accurate, complete, legible and timely reports to the Sponsor, as required. These include, but are not limited to, reports of any changes that significantly affect the conduct or outcome of the trial or increase risk to study participants. Safety reporting will occur as previously described. At the completion of the trial, the Lead Investigator will provide a final report to the Sponsor.

### **14.19 Audits**

The Sponsor has an obligation to ensure that this trial is conducted according to good clinical research practice guidelines and may perform quality assurance audits for protocol compliance. The Lead Investigator and authorized staff from the Lead Node; the National Institute on Drug Abuse Clinical Trials Network (NIDA CTN, the study sponsor); NIDA's contracted agents, monitors or auditors; and other agencies such as the Department of Health and Human Services (HHS), the Office for Human Research Protection (OHRP) and the Institutional Review Board of record may inspect research records for verification of data, compliance with federal guidelines on human participant research, and to assess participant safety.

## **14.20 Study Documentation**

Each participating site will maintain appropriate study documentation (including medical and research records) for this trial, in compliance with ICH E6 R2 and regulatory and institutional requirements for the protection of confidentiality of participants. Study documentation includes all case report forms, workbooks, source documents, monitoring logs and appointment schedules, sponsor-investigator correspondence, and signed protocol and amendments, Ethics Review Committee or Institutional Review Board correspondence and approved consent form and signed participant consent forms. As part of participating in a NIDA-sponsored study, each site will permit authorized representatives from NIDA and regulatory agencies to examine (and when permitted by law, to copy) clinical records for the purposes of quality assurance reviews, audits, and evaluation of the study safety, progress, and data validity.

Source documents include all recordings of observations or notations of clinical activities and all reports and records necessary for the evaluation and reconstruction of the clinical research study. Whenever possible, the original recording of an observation should be retained as the source document; however, a photocopy is acceptable provided that it is a clear, legible, and exact duplication of the original document.

## **14.21 Protocol Deviations**

This protocol defines a protocol deviation as any noncompliance with the clinical trial protocol. The noncompliance may be either on the part of the participant, the investigator, or the study site staff. As a result of deviations, corrective actions will be developed by the site and implemented promptly.

These practices are consistent with ICH GCP:

- Section 4.5 Compliance with Protocol, subsections 4.5.1, 4.5.2, and 4.5.3
- Section 5.1 Quality Assurance and Quality Control, subsection 5.1.1
- Section 5.20 Noncompliance, subsections 5.20.1, and 5.20.2.

Any departure from procedures and requirements outlined in the protocol will be classified as either a major or minor protocol deviation. The difference between a major and minor protocol deviation has to do with the seriousness of the event and the corrective action required. A minor protocol deviation is considered an action (or inaction) that by itself is not likely to affect the scientific soundness of the investigation or seriously affect the safety, rights, or welfare of a study participant. Major protocol deviations are departures that may compromise the participant safety, participant rights, inclusion/exclusion criteria or the integrity of study data and could be cause for corrective actions if not rectified or prevented from re-occurrence. Sites will be responsible for developing corrective action plans for both major and minor deviations as appropriate. Those corrective action plans may be reviewed/approved by the Lead Node and the CCC with overall approval by the IRB of record as needed. All protocol deviations will be monitored at each site for (1) significance, (2) frequency, and (3) impact on the study objectives, to ensure that site performance does not compromise the integrity of the trial.

All protocol deviations will be recorded [in the Electronic Data Capture (EDC) system via the Protocol Deviation CRF. The CCC, DSC and the Lead Investigator must be contacted immediately if an unqualified or ineligible participant is randomized into the study.

Additionally, each site is responsible for reviewing the IRB of record's definition of a protocol deviation or violation and understanding which events need to be reported. Sites must recognize that the CTN and IRB definition of a reportable event may differ and act accordingly in following all reporting requirements for both entities.

#### **14.22 Safety Monitoring**

The PI and/or Co-I will review or provide consultation for each Adverse Event (AE) and Serious Adverse Event (SAE) as needed. These reviews will include an assessment of the possible relatedness of the event to the study intervention or other study procedures. The PI and/or Co-I will also provide advice for decisions to exclude, refer, or withdraw participants as required. In addition, NIDA will assign a Safety Monitor/Medical Monitor to this protocol to independently review the safety data, present it to the DSMB for periodic review, and provide PIs a Safety Letter when necessary. The Safety Monitor/Medical Monitor will determine which safety events require expedited reporting to NIDA, the DSMB and regulatory authorities. This will include events that are serious, related and unexpected. The study staff will be trained to monitor for and report AEs and SAEs.

Each of the sites has established practices for managing medical and psychiatric emergencies, and the study staff will continue to utilize these procedures. Treatment providers at each site will be responsible for monitoring participants for possible clinical deterioration or other problems, and for implementing appropriate courses of action.

#### **14.23 Data and Safety Monitoring Board (DSMB)**

An independent CTN DSMB will examine accumulating data to assure protection of participants' safety while the study's scientific goals are being met. The CTN DSMB is responsible for conducting periodic reviews of accumulating safety and efficacy data. It will determine whether there is support for continuation of the trial, or evidence that study procedures should be changed, or if the trial should be halted, for reasons relating to the safety of the study participants, the efficacy of the treatment under study, or inadequate trial performance (e.g., poor recruitment).

##### **14.23.1 Safety Monitor / Medical Monitor**

The CCC Safety Monitor/Medical Monitor is responsible for reviewing all adverse events and serious adverse events reported. All SAEs will be reviewed within one business day of being reported in eClinical. The Safety Monitor/Medical Monitor will also indicate concurrence or not with the details of the report provided by the site. Where further information is needed, the Safety Monitor/Medical Monitor will discuss the event with the site. Reviews of SAEs will be conducted in the Advantage eClinical data system and will be a part of the safety database. All AEs are reviewed on a regular basis to observe trends or unusual events.

The CCC Safety Monitor/Medical Monitor will summarize each SAE and will provide a report to the LN and NIDA CCTN. If an event meets the criteria for FDA-defined expedited reporting, the CCC safety team and regulatory team will work together to submit an expedited safety report to the FDA. A copy of the expedited report will be submitted to the DSMB through the DSC. Other safety reports will be generated and presented at the scheduled Data Safety Monitoring Board (DSMB) meetings.

#### **14.24 Adverse Events (AEs)**

The Site PI or Co-I will review or provide consultation for each AE/SAE, as needed. These reviews will include an assessment of the possible relatedness of the event to the study intervention or other study procedures. The Site PI or Co-I will also provide advice for decisions to exclude, refer, or withdraw participants as required. In addition, NIDA will assign a Medical Monitor to this protocol to independently review the safety data, present it to the DSMB for periodic review, and provide PIs a Safety Letter when necessary. The Medical Monitor will determine which safety events require expedited reporting to NIDA, the DSMB, pharmaceutical, and regulatory authorities. This will include events that are serious, related, and unexpected. The study staff will be trained to monitor for and report AEs and SAEs. Additionally, as applicable, sites will submit reporting of AEs/SAEs according to IRB requirements. Each of the sites has established practices for managing medical and psychiatric emergencies, and the study staff will continue to utilize these procedures. Treatment providers at each site will be responsible for monitoring participants for possible clinical deterioration or other problems, and for implementing appropriate courses of action.

Safety for this study will be monitored through specific study assessments and medical record abstraction in addition to more standard AE/SAE reporting.

Depression/Suicidality: The PHQ-9 will be assessed at baseline and at 7 and 30 days post enrollment for the RCT. If the answer to question the question, “Over the past two weeks, how often have you been bothered by thoughts that you would be better off dead or of hurting yourself in some way?” is greater than “Not at all,” research staff will activate local procedures to ensure participant safety. The policies and procedures at that ED regarding assessment by a qualified clinician before leaving will be specified in the site clinical SOP.

Injection Site Examination: Participants will be asked to immediately report any unanticipated injection site reactions to study staff for evaluation, monitoring, and possible referral, as needed. Injection site reactions will be documented on the Injection Site Abnormality form.

##### **14.24.1 Adverse Events and Serious Adverse Events**

Adverse events will be captured and reported through the Adverse Event reporting mechanisms described in Section 18.0.

Events including withdrawal, injection site reactions, assessments for suicide risk, overdose and vital signs do not need to be reported as Adverse Events and will be captured on specific study forms. If any of these events meet the definition of a Serious Adverse Event described in Section 18.0, then they would be reported on an AE/SAE form set.

The reporting period for the randomized controlled trial begins at study product administration and ends at the last study visit, day 30 after the study injection, and the reporting period for the ancillary study begins at study product administration and ends at day 7.

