| Critical Action Checklist Implementation/Process Outcome |      | RA*     | Not an RCT participant outcome. Collected at Index ED Visit 1 in DSC database as part of RCT protocol. |                                                                             |                     |                      |
| Mental Health Assessment (MHA)                           |      | RA      |                                                                                                        | X (if participant endorse suicidality on Heath Status Form; PHQ-9 question) |                     |                      |
| Precipitated Withdrawal (PWD)                            |      |         |                                                                                                        | X                                                                           |                     |                      |
| Worsening Withdrawal Medications (WWM)                   |      |         |                                                                                                        | X                                                                           |                     |                      |
| Study Completion                                         |      |         |                                                                                                        |                                                                             |                     | X                    |
| Serious Adverse Event (Death)                            |      | RA      | X                                                                                                      |                                                                             |                     |                      |
| Protocol Deviations                                      |      | RA      | X                                                                                                      |                                                                             |                     |                      |

\* Site staff (RA), with PI input as needed.

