### 8.9.4 Adverse Events (AEs) and Serious Adverse Events (SAEs)

Adverse events will be captured and reported through the Adverse Event (AE) reporting mechanisms described in Section 18. Events including withdrawal (except for precipitated withdrawal), injection site reactions, assessments for suicide risk, overdose and vital signs do not need to be reported as Adverse Events and will be captured on specific study forms. If any of these events meet the definition of a SAE described in Section 18, then they would be reported on the AE/SAE forms set.

The reporting period for AEs and SAEs for the RCT starts at XR-BUP administration and ends at the last study visit, day 30 after enrollment.

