| Mental Health Assessment (MHA)             |      | RA      |                   | X (if participant endorse suicidality on Heath Status Form; PHQ-9 question) |                  |                     |
| Adverse Events                             | X    |         |                   |                                                                             |                  |                     |
| Serious Adverse Events                     | X    |         |                   |                                                                             |                  |                     |
| Protocol Deviations                        | X    |         |                   |                                                                             |                  |                     |

*\*As a last resort, Day 7 assessments may be completed by phone except for UDS and COWS.*

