## Site's Role in Eliciting and Reporting Adverse Events

Appropriately qualified and trained personnel will elicit participant reporting of AEs and SAEs at each study visit designated to collect AEs. Adverse events (medical and/or psychiatric) assessment will initiate with participant consent and follow-up of reported AEs will continue through 30 days post last study visit for RCT and through 7 days for ancillary components. Study personnel will obtain as much information as possible about the reported AE/SAE to complete the AE/SAE forms and will consult as warranted.

Standard reporting, within 7 days of the site becoming aware of the event, is required for reportable AEs. Expedited reporting (within 24 hours of their occurrence and/or site's knowledge of the event) is required for reportable SAEs (including death and life-threatening events). Local sites are responsible for reporting SAEs to the IRB of record, per the IRB of record's guidelines.

Sites are required to enter reportable AEs and SAEs in the Advantage eClinical system. The AE form is used to capture reportable AEs and SAEs (as defined in the protocol). Additional information may need to be gathered to evaluate SAEs and to complete the appropriate CRFs and the summary. This process may include obtaining hospital discharge reports, medical records, autopsy records or any other type records or information necessary to provide a complete and clear picture of the serious event and events preceding and following the event. If the SAE is not resolved or stable at the time of the initial report or if new information becomes available after the initial report, follow-up information must be submitted as soon as possible.

Reportable adverse events will be followed until resolution, stabilization or study end. Any serious adverse reactions will be followed until resolution or stabilization even beyond the end of the study.

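### Protocol 14.24.1 drops the exception that makes precipitated withdrawal a reportable AE, and RCT Table 2 schedules only deaths, so whether a non-serious case enters the AE tables can differ by site

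*Combined protocol and SAP*

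**What the plan says.** Three protocol sections list events that need no AE report because other forms capture them.

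- Section 8.9.4, for the RCT: "Events including withdrawal (except for precipitated withdrawal), injection site reactions, assessments for suicide risk, overdose and vital signs do not need to be reported". Precipitated withdrawal is taken out of the exemption, so it is reportable.
- Section 9.11.29, for the ancillary study, carries the same exception.
- Section 14.24.1: "Events including withdrawal, injection site reactions, assessments for suicide risk, overdose and vital signs do not need to be reported as Adverse Events". The exception is absent. The section closes by setting reporting periods for both the RCT and the ancillary study, so it governs the same two components.

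All three keep serious events reportable; 14.24.1 does so with "If any of these events meet the definition of a Serious Adverse Event described in Section 18.0". All three also refer the reader to Section 18, which says "The AE form is used to capture reportable AEs and SAEs (as defined in the protocol".

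The two schedules differ as well. In RCT Table 2 the only AE or SAE row is "Serious Adverse Event (Death", although the table also has a row for the dedicated form, "Precipitated Withdrawal (PWD". Ancillary Table 3 has general rows for adverse events and for "Serious Adverse Events".

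In the SAP, section 8.2.1 summarises treatment-emergent AEs by arm with severity and relatedness. Section 8.2.4 gives a separate by-arm table and a listing of precipitated withdrawals.

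**The concern.** The same non-serious event is reportable under one section and exempt under another, and the section that both cite does not decide between them. The RCT is planned at approximately 25 sites, so mixed practice is a realistic risk.

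The AE label carries consequences. Under Section 18, a study medical clinician reviews reportable AEs for seriousness, severity and causality at least weekly, and sites report them within 7 days. Under 14.23.1 the medical monitor reviews reported AEs for trends. The DSMB receives AE listings. By contrast, 8.9.2 describes the PWD form as recording whether the event occurred and when; it describes no severity grade and no relatedness judgement.

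A site that follows 14.24.1 literally would file the PWD form and no AE. The by-arm AE comparison would then depend partly on each site's reading, for the one event on which the RCT pausing rules rest. Any shortfall would probably fall mainly in the XR-BUP arm, since 8.4.11 frames precipitated withdrawal as an XR-BUP event. The AE table and the precipitated withdrawal table could also disagree in the final report with nothing to explain the difference.

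**Working it through.** The plan states no figure on this point, so the check is a comparison of the texts, followed by a size illustration.

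**Step 1. What each source requires.**

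| Source | Component | Non-serious precipitated withdrawal | Non-fatal SAE |
|---|---|---|---|
| 8.9.4 | RCT | AE report | Report |
| 9.11.29 | Ancillary | AE report | Report |
| 14.24.1 | Both | No AE report, on its wording; study form only | Report |
| Section 18 | Both | Whatever the protocol makes reportable | Report |
| Table 2 | RCT | No AE row; PWD form row present | No row; deaths only |
| Table 3 | Ancillary | AE row | SAE row |

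The third column disagrees between 8.9.4 and 14.24.1 for the RCT, and between 9.11.29 and 14.24.1 for the ancillary study. Section 18 points back to the protocol, so it cannot break the tie. Table 2 conflicts with both 8.9.4 and 14.24.1, because even the shorter rule requires non-fatal SAEs.

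**Step 2. Which outputs depend on the reading.**

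- Dependent: the AE tables and AE listing in SAP 8.2.1, the corresponding ancillary AE outputs in SAP 8.1.3, the AE listings sent to the DSMB, and the weekly clinician review of reportable AEs.
- Not dependent: SAP 8.2.4 (table and listing of precipitated withdrawals), the ancillary safety-event table in SAP 8.1.1 (its shell, Table 20, counts from the PWD form), SAE reporting, and the pausing rules in protocol 8.4.12, which count events and not AE forms.

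**Step 3. Size illustration for the RCT.**

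Inputs: about 2,000 participants (protocol 12.3) and 1:1 allocation (8.4.4). The event rate is an assumption, because the documents give none for the RCT. I use 1% to 8%, where 8% is the later-stage pausing threshold in 8.4.12.1.

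- XR-BUP arm: 2,000 × 1/2 = 1,000
- Lower end: 0.01 × 1,000 = 10 events
- Upper end: 0.08 × 1,000 = 80 events

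This is an upper range, since it treats every event as non-serious and every site as omitting the AE record. If sites enrolling half of the arm omitted it, the range would be 5 to 40.

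**The case against.** The strongest reply is that this is a missing parenthesis with little effect. The sentence in 14.24.1 goes on to say that the exempt events are captured on specific study forms, and precipitated withdrawal has such a form. The SAP tabulates the event separately in both components. In the ancillary study, protocol 9.12 sends every physician-determined case to team review that includes the designated medical monitor, whatever its AE status, and SAP 7.1.1 adds adjudication by study consultants. The two component-specific sections agree, so reading the general section in line with them is natural. A schedule row is also not a reporting rule: 8.9.4, 14.24.1 and Section 18 all call for AE reporting, and an AE form exists.

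Most of this stands, and it limits the point to AE records for non-serious events. It does not remove the conflict. Nothing in the protocol ranks 8.9.4 above 14.24.1, and the PWD form as described does not carry the grading and relatedness that SAP 8.2.1 reports.

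The documents do not support three stronger readings that a reader might infer:

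- *The hazard itself goes uncounted, or the pausing rules fail.* The PWD form, SAP 8.2.4 and 8.4.12 show otherwise.
- *Table 2 means that no non-fatal AE is collected in the RCT.* A site would have to disregard 8.9.4, 14.24.1 and Section 18 together.
- *The ancillary study could lose up to 7 of 75 cases, the largest count under 10%.* Protocol 12.6.6 and SAP 7.1.2 apply the 10% criterion to the upper 95% Clopper-Pearson limit. At n = 75, 2 events give an upper limit of 9.3%, 3 give 11.2% and 7 give 18.3%, so at most 2 events meet it. That criterion is also not a cap on how many events can occur.

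**Conclusion.** The inconsistency is real and is wrong as written. It lies between 14.24.1 and both 8.9.4 and 9.11.29, with Table 2 out of line with all RCT reporting text. It affects whether non-serious precipitated withdrawals appear in the AE tables and listings with a severity grade and relatedness, and whether they pass through AE-based review. It does not affect the by-arm count of precipitated withdrawals, serious event reporting, the pausing rules or any effectiveness analysis.

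The size cannot be fixed from the documents. The 10 to 80 events in about 1,000 XR-BUP participants rest on an assumed rate, and the 80 corresponds to a pausing threshold, not a forecast. The actual effect also depends on how many sites follow 14.24.1, which the documents do not show.

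**What to change.** 1. In protocol 14.24.1, insert after the word withdrawal the same parenthetical exception that 8.9.4 and 9.11.29 carry, so that one rule holds throughout.
2. In RCT Table 2, change the death-only row to Adverse Events / Serious Adverse Events, in line with 8.9.4 and with ancillary Table 3.
3. In SAP 8.2.1, add a step before the tables are run: list every participant whose PWD form records a precipitated withdrawal, check for a matching AE record, and query the site where there is none.

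The cost is protocol wording, one reconciliation listing and possibly some late AE forms for cases already on the PWD form. The SAP revision history shows version 4.0, meant to finalise the RCT sections before database lock, with no approval date yet, so on the documents step 3 can still be added for the RCT.
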